## Abstract

**Background:**

Bioactive compounds, such as human milk oligosaccharides (HMOs), impact the development of the intestinal microbiome and immune maturation in early life. They have been shown to result in positive benefits, including improved gut health, reduced frequency of infections, and age-appropriate growth when added to infant formula. However, data supporting the added value of including these HMOs in early-stage infant formula is currently lacking among Chinese infants.

**Objective:**

In this double-blind randomized controlled trial including a nonrandomized reference breastfed group, we will test the efficacy of ready-to-feed infant formula containing 2 HMOs (2-fucosyllactose and lacto-N-neotetraose) on *Bifidobacteria* abundance, gut microbiome, gut and immune health, growth, and quality of life.

**Methods:**

Healthy infants will be enrolled between 3 and 14 days after birth at 5 sites in China and randomized to either the experimental group (fed ready-to-feed infant formula containing 2 HMOs) or the control group (fed the same ready-to-feed infant formula without the 2 HMOs), using a dynamic allocation algorithm with double blinding. Infants will receive trial formula until age 6 months and will be followed up until age 12 months. The breastfed group will serve as a reference. The primary end point will be *Bifidobacteria* abundance in fecal samples at 3 months, measured via quantitative polymerase chain reaction. Secondary end points will include fecal microbiome (including taxonomy, diversity, functionality, and metabolites), fecal markers of immune health, gastrointestinal tolerance, stooling patterns, immune competence (overall state of the immune system), sleep quality, growth, quality of life, medication use, and physician-reported adverse events. A 2-sided test at the 5% significance level will be used for statistical testing.

**Results:**

The study received ethical approval in March 2024 and will be completed by the end of 2026, which will be followed by a publication in a peer-reviewed journal.

**Conclusions:**

The Starter Liquid Infant Formula Trial (STARLIT) will be one of the first to assess the efficacy of these 2 HMOs among Chinese infants on gut and immune health, in addition to clinically relevant outcomes such as quality of life, growth, and adverse events. This study should help to demonstrate that an increase in the growth of beneficial *Bifidobacteria* in response to intake of 2-fucosyllactose and lacto-N-neotetraose may have a broader impact on overall gut microbiome composition and infant gut and immune health.

**Trial Registration:**

ClinicalTrials.gov NCT06361719; https://clinicaltrials.gov/study/NCT06361719

**International Registered Report Identifier (IRRID):**

PRR1-10.2196/66489

## Introduction

Human milk provides an abundance of structurally diverse bioactive compounds that promote appropriate gut maturation through their effects on the gut microbiome, gut barrier function, and intestinal immunity [1-8]. These bioactive compounds include human milk oligosaccharides (HMOs), α-lactalbumin, osteopontin, lactoferrin, gangliosides, phospholipids, immunoglobulins, and sphingomyelin [5-7,9]. Specifically, HMOs play a crucial role in the development of the intestinal microbiome and immune maturation [10,11] as they promote the colonization of beneficial bacteria such as *Bifidobacteria* [12,13] and improve gut epithelial barrier function by preventing the uptake of pathogens and toxins in the gut [13]. More specifically, 2-fucosyllactose and lacto-N-neotetraose have been found to enhance fermentation by gut microbes [14] and have antibacterial [15,16], antiviral [17,18], and anti-inflammatory activities [17] in vitro. In preclinical models, 2-fucosyllactose and lacto-N-neotetraose enhance fermentation and short-chain fatty acids production [18] by the gut microbiome [14] by promoting the growth of the beneficial *Bifidobacterium* species [15-19], while inhibiting colonization by pathogenic bacteria [18-20]. Preclinical evidence also suggests that 2-fucosyllactose and lacto-N-neotetraose exhibit antibacterial action beyond the gut, specifically the upper respiratory tract [21,22], as well as demonstrating antiviral [23,24] and anti-inflammatory activity [19,20,24].

Term infant formula supplemented with up to 1.0 g/L of 2-fucosyllactose alone [25,26] or in combination with 0.5 g/L of lacto-N-neotetraose [27] is well tolerated and supports normal growth. Infants fed formula supplemented with 1.0 g/L 2-fucosyllactose and 0.5 g/L of lacto-N-neotetraose in the first 6 months of life had lower parent-reported morbidity, including bronchitis and lower respiratory tract infections (LRTI) through the first 12 months of life compared to infants fed the same cow’s milk–based infant formula without HMOs [27]. Additionally, lower antipyretics at age 4 months and antibiotics at ages 6 and 12 months were recorded in the HMO-fed group [27].

Part of the observed benefits of 2-fucosyllactose and lacto-N-neotetraose consumption in early life may be mediated by the effects of these 2 HMOs on the maturing gut microbiome. Consumption of 2-fucosyllactose and lacto-N-neotetraose containing formula in early life was associated with higher abundance of fecal *Bifidobacteriaceae* compared to non-HMO containing formula [28] and a gut microbiome composition closer to that of the breastfed group (BG), characterized by a greater likelihood to have a fecal community type similar to the most predominant of breastfed infants (defined by a high abundance of *Bifidobacteriaceae*). The latter was associated with lower antibiotic usage [28] and a distinct gut microbiome signature associated with reduced incidence of LRTI [29]. Finally, extensively hydrolyzed whey–based formula supplemented with these HMOs (2-fucosyllactose and lacto-N-neotetraose) was also demonstrated to support normal growth, have good gastrointestinal tolerance [30], reduce the frequency of upper respiratory tract and ear infections [30], increase fecal *Bifidobacterium*, and delay shift to an adult-type microbiome in infants with cow’s milk protein allergy [31].

These findings support the rationale for supplementing cow’s milk–based infant formulas with HMOs, including 2-fucosyllactose and lacto-N-neotetraose, for use in infants where either breastfeeding or the provision of breastmilk is not possible. However, data are currently lacking in Chinese infants as to how these HMOs can positively impact them very early in life. More specifically, clinical substantiation on the impact of these 2 HMOs on the dynamic changes in gut microbiome, gut barrier integrity, immune response, and other developmental outcomes is warranted in this population.

We aim to conduct a double-blind randomized controlled trial including a nonrandomized, reference BG to assess the efficacy of a ready-to-feed, liquid, bovine milk–based whey, predominant term infant formula containing 2-fucosyllactose and lacto-N-neotetraose from the first 2 weeks of age up to age 6 months in Chinese infants. We will also study its effects postintervention for up to age 12 months in promoting appropriate gut maturation and supporting immune functions. The primary objective of this trial is to show an increase in *Bifidobacteria* abundance in the experimental group (EG, which will receive ready-to-feed infant formula containing 2 HMOs) compared to the control group (CG, which will receive the same ready-to-feed infant formula without the 2 HMOs) at age 3 months. Secondary objectives include comparing the following outcomes among all the feeding groups (EG, CG, and BG): fecal microbiome and metabolic profile, fecal markers of immune health, gut barrier integrity, and inflammation, gastrointestinal tolerance, adverse events (AEs), infant immune competence, infant sleep quality, infant growth, and infant quality of life from enrollment up to age 12 months.

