**Figure 1 figure1:**
[figure not shown]
Graphical representation of the 3-arm study design. Randomization is for the formula-fed group only. 2’FL: 2-fucosyllactose; BG: breastfed group; CG: control group; EG: experimental group; HMO: human milk oligosaccharide; LNnT: lacto-N-neotetraose; RTF: ready-to-feed; V: visit.

**Table 1 table1:** Study sessions and procedure.

Procedures			Intervention period													Observation period						
			V1^a^		H1^b^		H2		V2		H3		V3		H4			V4		H5		V5
Informed consent			✓																			
Inclusion and exclusion criteria			✓																			
Physical examination			✓																			✓
Medical history			✓																			
Demographics			✓																			
Anthropometry			✓						✓				✓					✓				✓
Randomization			✓																			
Fecal samples					✓		✓				✓				✓					✓		

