**Inclusion criteria**
Singleton, healthy, full-term gestational birth (≥37 completed weeks of gestation), with a birth weight ≥2.5 kg and ≤4.5 kg and postnatal age of 3-14 days (date of birth=day 0), inclusive.Willing and able to comply with scheduled visits and the requirements of this trial protocol.Access to a working freezer.For the formula-fed groups: infant is exclusively consuming and tolerating a cow’s milk infant formula for at least 3 days before enrollment. The infant’s mother has independently elected not to breastfeed.For the breastfed reference group: the infant has been exclusively consuming breastmilk since birth, and the infant’s mother has decided to continue until at least age 3 months.

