### Additional Variables of Interest

#### Demographic Data, Birth, and Household Characteristics

Demographic data including age of child, sex, ethnicity, birth characteristics (birth weight and length, gestational age at birth, parity), APGAR (appearance, pulse, grimace, activity, and respiration) score at 5 minutes, feeding history (eg, breastmilk, formula, or complementary feedings), maternal age, education, health history and family history of allergy will be collected from the participant or parents or LARs at the enrollment visit (V1).

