For all categorical and continuous variables, appropriate descriptive statistics will be calculated by visit, feeding groups, and delivery mode. The primary end point of the difference in *Bifidobacteria* abundance between EG and CG infants will be analyzed using analysis of covariance (ANCOVA), correcting for baseline, site, gender, and mode of delivery. If the investigation of data reveals an inflation of the null values (no detected *Bifidobacteria* in samples), then the ANCOVA model will be replaced by a 0-inflated mixture model. For continuous secondary end points, ANCOVA models correcting for baseline, site, gender, and delivery will be used for analyses. For categorical secondary end points, logistic regression models will be used to compare between feeding groups at each time point separately. Fecal metabolism and immune health markers will be analyzed according to dry stool weight, using an ANCOVA model at each time point to compare between feeding groups, correcting for baseline, site, gender, and mode of delivery. The necessity to log-transform the end points or to use nonparametric methods will be assessed during the blind data review and addressed in the statistical analysis plan. During the final analysis, the models may be modified to a mixed model repeated measurements to consider the longitudinal nature of the data. AEs will be compared between feeding groups using the Fisher exact test.

Missing data will be assumed to be missing at random unless the blind review of the data demonstrates a pattern of missingness, in which case, multiple imputation for the primary outcome of *Bifidobacteria* abundance at 3 months may be used. In the case of outliers for any end point, robust approaches or sensitivity analyses may be used. Statistical testing for all end points will be 2-sided and at a 5% significance level. All statistical analyses will be performed in SAS Life Science Analytics Framework (version 5.4.1; SAS Institute Inc).

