Our study has several strengths. Its double-blinded design will ensure blinding of the participants, investigators, data collectors, outcome assessors, and data analysts to minimize bias in the reporting of the study outcomes. The study will be conducted across 5 different sites representing a wide geography within China and enabling a nonpreceded characterization of the effects of HMO supplementation in this population. Regarding the intervention products, the administration of a control formula identical to the test formula, apart from its HMO content, would allow us to clarify the efficacy of supplementation by 2-fucosyllactose and lacto-N-neotetraose with no further nutritional confounding factors. Yet, the 2 formulas must be precisely fully compliant with infant nutritional needs at this age. The nonrandomized BG will serve as a reference and help to gain insights into the contribution of these HMOs in shifting the gut microbiome and all other developmental outcomes closer to those of breastfed infants. The benefit of breastfeeding will be discussed with all parents who will meet a qualified lactation consultant before enrollment to ensure that they make an informed decision that is best for their infant. The service of a lactation consultant will be available over the course of the study to allow any parent to switch to breastfeeding at any time point.

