The prospective and longitudinal nature of this study will allow us to collect detailed information on a comprehensive set of outcomes during the first year of life. Importantly, the fecal microbiome will be profiled using the most advanced and standard methodologies, such as NGS, in addition to quantitative polymerase chain reaction. This should enable us to shed light on the effects of HMOs on the dynamic maturation of the gut microbiome of Chinese infants at the taxonomic but also functional levels. HMO-mediated microbiome modulation of immune system development and fitness will be carefully monitored. We will capture infant illness weekly for 1 year using an IID, providing great granularity over AE occurrence. These IIDs will be used to generate an automated diagnosis that will be reviewed and confirmed by a study physician. Additionally, for the first time, we will use a novel Pediatric Immune System Index to assess immune competence that will allow the detailed characterization of gastrointestinal, upper respiratory tract infection, LRTI, and skin allergies by recording the duration, number of episodes, severity of health care visits, and treatment received. To complement this, fecal immune markers will also be quantified. Furthermore, we will be using validated questionnaires to capture details about gastrointestinal symptoms, sleep patterns, and quality of life to enhance our understanding of the effect of HMOs and their microbiome-modulating properties on infants’ well-being [27]. Importantly, we will also collect covariates, including maternal education, delivery mode, family history of allergy, infant dietary intake, and infant feeding (breastfeeding and formula feeding), medications, and treatments to adjust our analysis for potential confounding effects. In our study, the randomization is stratified by delivery mode. We hope to gain important insights into the effect of HMO supplementation, particularly among infants born by CS, in whom lower colonization rates of beneficial bacteria such as *Bifidobacterium* and *Bacteroides*, and higher colonization rates of *Clostridium*, *Lactobacillus*, *Enterobacter*, *Enterococcus*, and *Staphylococcus* have been reported [62]. This is particularly relevant considering the high rates of elective CS in China with an increase reported from 28.8% in 2008 to 36.7% in 2018 [63] and reaching up to 43.79% in 2019 according to the data published by the National Health Service and Quality Safety Report (obstetrics) in 2020 [64] This is far above the CS rates of 10%-15% of all deliveries suggested as reasonable by the WHO [65,66] and likely impacts the immune development of their infants, risk for allergy, atopy, and asthma, and intestinal gut microbiome diversity [67].

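### Adverse events in the self-selected breastfed group are to be tested against the formula arms with Fisher's exact test, which cannot carry the confounder adjustment the protocol says it collects data for

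*Protocol article*

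**What the plan says.** The secondary objective at the end of the Introduction is "comparing the following outcomes among all the feeding groups (EG, CG, and BG", and AEs are on the list that follows. The Statistical Analysis section uses the same term for the group factor: "AEs will be compared between feeding groups using the Fisher exact test". It sets a two-sided 5% level for all end points, and its safety set includes breastfed infants. For categorical secondary end points it says that "logistic regression models will be used to compare between feeding groups at each time point separately".

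BG stands outside the allocation. The Figure 1 legend states "Randomization is for the formula-fed group only", and the Inclusion criteria admit a breastfed infant whose "mother has decided to continue until at least age 3 months". The Discussion says "The nonrandomized BG will serve as a reference".

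On confounding, the Discussion says that maternal education, delivery mode, family history of allergy, diet and feeding are collected, together with "medications, and treatments to adjust our analysis for potential confounding effects". The section on demographic data confirms that "maternal age, education, health history and family history of allergy will be collected" at the first visit.

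**The concern.** The protocol gives a group formed by maternal choice the same AE test as the two randomized arms. Balancing on site, sex and delivery mode applies only to EG and CG. Mothers who breastfeed exclusively may differ from those who formula-feed in education, mode of birth, allergy history or other factors that bear on infant illness. Fisher's exact test compares crude proportions and has no place for such factors.

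The AE data also start with a weekly illness diary kept by parents. BG parents necessarily know how their infant is fed. The article does not state this, but breastfeeding cannot be masked, and the blinding it describes concerns the identity of the formula.

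At stake is how the safety tables will be read. A small p-value for formula against breast milk could arise with no effect of feeding, or a real difference could be masked. It would look the same in print as the p-value for the randomized EG-CG contrast. The limitations paragraph does not mention confounding in the comparisons with BG.

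**Working it through.** **Does the AE test include BG?** The Introduction defines the feeding groups as EG, CG and BG. The section on Bifidobacteria abundance uses a different term, intervention groups, for EG and CG alone. The AE sentence uses feeding groups. On the article's own vocabulary, BG is in the test.

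**Can the test deliver the stated adjustment?** Fisher's test on a 2×2 table conditions only on the table margins. None of the covariates named in the Discussion can enter it. So the article states an intention to adjust and, for AEs, names a method that cannot do so.

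**How large could the effect be?** The protocol gives no AE rates and no covariate distributions, so it has no figure of its own to reproduce. What follows is an illustration.

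Inputs from the Sample Size section: 105 infants per formula arm and 52 in BG. From the Statistical Analysis section: two-sided 5%. Everything else is assumed: one binary risk factor, its prevalence in each group, the AE risk with and without it, and no effect of feeding.

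Group AE risk = prevalence × risk with factor + (1 − prevalence) × risk without factor.

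- Case A, prevalence 60% formula and 30% BG, AE risk 50% with and 30% without: formula 0.6×0.5 + 0.4×0.3 = 0.42; BG 0.3×0.5 + 0.7×0.3 = 0.36; difference 6 points.
- Case B, same prevalences, AE risk 60% and 30%: formula 0.6×0.6 + 0.4×0.3 = 0.48; BG 0.3×0.6 + 0.7×0.3 = 0.39; difference 9 points.
- Case C, prevalence 70% and 30%, AE risk 60% and 30%: formula 0.7×0.6 + 0.3×0.3 = 0.51; BG 0.39; difference 12 points.

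Rejection probability = the sum, over all pairs of event counts, of the product of the two binomial probabilities wherever Fisher's two-sided p is at most 0.05:

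| Formula vs BG risk (105 vs 52) | Rejection |
|---|---|
| 40% vs 40% (no confounding) | 3.9% |
| 42% vs 36% (A) | 8.8% |
| 48% vs 39% (B) | 16.1% |
| 51% vs 39% (C) | 26.5% |

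**Sensitivity.** These cases need a 30- to 40-point imbalance in a factor that multiplies AE risk by 1.67 to 2. With a 20-point imbalance (44% vs 24%), a base risk of 20% to 30% and a risk ratio of 1.5 to 2.0, rejection is 4.3% to 8.9%. With a base risk of 20%, a risk ratio of 1.5 and a 10-point imbalance (44% vs 34%), it is 3.9%, which is no visible inflation.

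**The case against.** The strongest reply has four parts.

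- **BG is openly a nonrandomized reference.** The article says so repeatedly, and a careful reader will discount the contrasts. This is true, but the label does not take BG out of the AE objective or the AE test.
- **AEs are not raw parent reports.** Diary entries are reviewed, and a trial physician validates symptoms and diagnoses. This reduces the reporting concern. It cannot recover events that parents did not record, and it does nothing about differences in background risk.
- **Fisher's test is conventional for sparse AE tables, and only 52 breastfed infants are planned.** A model with many covariates could be unstable or fail to converge. This stands, and it argues against requiring a long adjustment list for every AE.
- **The size rests wholly on assumptions.** This also stands. The 27% is the most extreme case shown and is not an estimate for this trial.

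A reader might also infer that the logistic models for categorical outcomes are unadjusted, because the neighbouring ANCOVA sentences list baseline, site, gender and delivery mode while the logistic sentence lists nothing. The documents do not support that. The sentence names no covariates but excludes none, the Discussion points towards adjustment, and the list may sit in the statistical analysis plan, which is not shown.

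**Conclusion.** The point holds for AEs. As written, EG-BG and CG-BG differences in AEs receive a two-sided 5% test that cannot adjust for the confounders the article says are collected for that purpose. The resulting p-values mix feeding with parental and birth differences.

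The mechanism follows from the text. Its size does not: the rise from about 4% to between 9% and 27% assumes a background difference of 6 to 12 points, and smaller imbalances give little or none.

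It would be wrong to conclude that the trial's safety comparison as a whole is compromised. The EG-CG contrast is randomized, and Fisher's test is valid there. The primary end point, also EG against CG, is not touched. For the logistic models, all that can be said is that no covariates are named. This is a correction that should be made, not a flaw in the main result.

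**What to change.** In the Statistical Analysis section:

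1. Restrict Fisher's exact test, and all AE p-values, to the randomized EG-CG comparison.
2. Report AE rates in BG, and EG-BG and CG-BG risk differences with 95% confidence intervals, without p-values. Label them observational.
3. Where event counts allow, adjust these differences for a short prespecified list of baseline factors already collected, such as site, delivery mode, maternal education and family history of allergy. Where events are too sparse, give the unadjusted interval and say so.
4. Use the same covariates in any logistic comparison that involves BG.

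The cost is a change of wording and some additional modelling, with no new data collection. The downsides are that there is no AE p-value against BG, and that intervals are somewhat wider or, for sparse events, unadjusted. The Results section reports 122 of the planned 262 infants recruited by June 2025, so on the article's account the change can be made before database lock and unblinding.
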